**Methods/Design:**

The research will target individuals who work on mixed farming enterprises and routinely using OPs (*n* = 50) and non-farmers (*n* = 30). Baseline data are collected regarding demographic, health conditions and behaviours, Kessler 10 (K10) scores, chemical use and personal protection. Baseline anthropometric measures include height, weight, hip and waist circumference, body fat analysis and, biochemical analysis of fasted total serum cholesterol, triglycerides, low-density cholesterol (LDL), high-density cholesterol (HDL) and blood glucose. Analysis of erythrocyte cholinesterase (EAChE) activity is also conducted using a finger prick test. Testing of EAChE is then repeated in all participants every 3 weeks for a maximum of three times over a period 10 weeks. Participants are provided with full feedback and counselling about their EAChE activity after each reading and a detailed summary provided to all participants at the completion of the study. Data will be analysed using repeated measures within a general linear model.

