### Aims

The Cholinesterase Research Outreach Project (CROP) will use clinical sampling to determine the level of exposure associated with the routine use of OPs by Victorian farmers and/or their workers. This preliminary study will examine the methodology of testing for EAChE activity at POC and provide evidence for future work by identifying the exposure patterns and pathways of individuals most at risk in farming communities. It is anticipated that CROP will inform future research studying pesticide exposure in farming communities.

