## Methods/design

### Evaluation design

To evaluate if a difference in cholinesterase activity was present in farmers before and after exposure, sample size is determined at the power of 80 % (β = 0.2) with α set at 0.05 for an effect size of one standard deviation. This requires the sample size to be a minimum of 30 farming individuals exposed to pesticides. By considering the probable retention rate (≥85 %) for a 7-month study, based on previous research in similar populations, [16] the target recruitment number is fixed at a target of 50 farmers.

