### Sample size and inclusions

Consent will be obtained from 80 participants recruited via existing contacts and industry groups, letterbox drops and newspaper articles from a number of farming and community groups, specifically;

Mixed farming enterprises and sheep dipping/spraying contractors (*n* = 50) who are using OPs and a convenience group of non-farming individuals (*n* = 30) from the rural community of Hamilton, Australia.

Participants need to have been farming for more than 5 years, be aged between 18 and 75 years, speak English, and not had a previous known chemical incident. Questionnaires will be used to determine whether or not they are the primary pesticide user. Any non-farming individuals tested must also be aged between 18 and 75 and have not had a previous chemical incident. Participants from both groups will be self-reported not pregnant, not suffering from a known chronic disorder, not taking anti-inflammatory drugs or supplements and not exercising excessively throughout the study.

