### Data entry, handling and statistical analysis

All data will be managed and analysed within the statistical program SPSS (IBM Corp. Released 2012 IBM SPSS Statistics for Windows, Version 21.0. Armonk, NY). SPSS is a statistical package widely used in quantitative social science research and is suitable for multivariate analysis. Data will be analysed using repeated measures (subjects as own controls) within the General Linear Model. Correlation coefficients between pesticide exposure and metabolic variables will be calculated using Pearson’s and Spearman’s correlation as appropriate. P values will be considered statistically significant at *p* < 0.05.

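### More than one participant per farm is allowed, but the stated model treats all people as independent and no farm identifier is listed, so the standard error of the EAChE change may be too small

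*Protocol article*

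**What the plan says.** **Model.** Under Data entry, handling and statistical analysis: "Data will be analysed using repeated measures (subjects as own controls) within the General Linear Model". Significance is set at p < 0.05. The section names no farm or household term.

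**Who can enrol.** The Aims refer to the "routine use of OPs by Victorian farmers and/or their workers". Sample size and inclusions describes the farmer group of 50 as "Mixed farming enterprises and sheep dipping/spraying contractors". The Abstract words it as people: "The research will target individuals who work on mixed farming enterprises and routinely using OPs". On the role of each participant: "Questionnaires will be used to determine whether or not they are the primary pesticide user". That status is recorded and is not an entry criterion. No rule limits enrolment to one person per farm or household.

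**How they are recruited.** Participants are "recruited via existing contacts and industry groups, letterbox drops and newspaper articles from a number of farming and community groups".

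**What is collected.** Survey methodology lists type of farming and residential postcode. Neither that section nor Table 1 lists a farm or household identifier.

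**Sample size.** Evaluation design sizes the study for the before/after difference in farmers: "sample size is determined at the power of 80 % (β = 0.2"), "with α set at 0.05 for an effect size of one standard deviation". It states a minimum of 30 and a recruitment target of 50.

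**The concern.** Two people working on one farm would plausibly use the same OP products on the same dates. The Background describes farm-level tasks (dipping, drenching, jetting, pasture spraying) and exposure in the home through laundry and storage. Their EAChE changes would then tend to move together, and a second person from a farm adds less information than a person from a different farm.

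A model whose only dependence is within subject counts both people in full. The standard error of the mean change is then too small, its confidence interval too narrow, and the p < 0.05 rule too liberal. Without a farm identifier this could be hard to repair after data collection, because a postcode does not identify a farm.

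**Working it through.** **1. The plan's own figure.** The inputs are 80% power, alpha 0.05 and a 1 SD effect on a before/after change. The paired normal formula gives n = (1.96 + 0.84)² / 1² = 7.8, so 8; the exact t calculation gives 10. The stated minimum is 30. A two-group formula gives 16 per group, 32 in total, which is close to 30 but is not the before/after design described. Allowing for 85% retention, 30 / 0.85 = 35.3, so 36, against a target of 50. How 30 and 50 were reached is a separate matter. What counts here is that 30 is well above what the stated effect needs.

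**2. The unit counted.** Consent is sought from 80 participants, and 50 + 30 = 80. The 50 are therefore people, despite the word for enterprises in the same section.

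**3. Effect of shared farms.** Let m be the number of participants per farm and ICC the within-farm correlation of EAChE change. The documents give neither, so both are assumed.

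- Design effect: DE = 1 + (m − 1) × ICC
- True SE / naive SE = √DE
- Real type I error of a nominal two-sided 5% test = 2 × [1 − Φ(1.96 / √DE)]
- Independent farmers that 30 farmers are worth = 30 / DE

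| m | ICC | DE | SE ratio | Type I error | 30 / DE |
|---|---|---|---|---|---|
| 1 | any | 1.00 | 1.00 | 5.0% | 30.0 |
| 1.5 | 0.05 | 1.025 | 1.01 | 5.3% | 29.3 |
| 1.5 | 0.1 | 1.05 | 1.02 | 5.6% | 28.6 |
| 1.5 | 0.3 | 1.15 | 1.07 | 6.8% | 26.1 |
| 1.5 | 0.5 | 1.25 | 1.12 | 8.0% | 24.0 |
| 2 | 0.1 | 1.10 | 1.05 | 6.2% | 27.3 |
| 2 | 0.3 | 1.30 | 1.14 | 8.6% | 23.1 |
| 2 | 0.5 | 1.50 | 1.22 | 11.0% | 20.0 |
| 3 | 0.1 | 1.20 | 1.10 | 7.4% | 25.0 |
| 3 | 0.3 | 1.60 | 1.26 | 12.1% | 18.8 |
| 3 | 0.5 | 2.00 | 1.41 | 16.6% | 15.0 |

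A simulated paired t-test on 42 farmers in clusters of 2 or 3, for ICC 0.1, 0.3 and 0.5, gave 6.0%, 8.7%, 11.2% and 7.3%, 12.1%, 16.7%, in agreement with the formula.

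The formula is exact for equal farm sizes. With unequal sizes, m should be the person-weighted mean Σm²/Σm. For example, if half the farms supply one person and half supply two, this is (1 + 4) / (1 + 2) = 1.67, and at ICC 0.5 DE = 1.33, the SE ratio is 1.15 and type I error is 9.0%. That does not change the picture.

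**4. Power.** With 30 independent farmers the paired test has 99.96% power for a 1 SD change. With 30 / DE farmers it has 98.9% or more at m = 2 and 94.9% at m = 3, ICC 0.5.

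**5. Correlations of exposure with metabolic variables.** The inflation for a correlation is roughly 1 + (m − 1) × ICC₁ × ICC₂, with one ICC for each variable. At m = 2 and 0.3 for each it is 1 + 0.09 = 1.09, against 1.30 for the mean change.

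**The case against.** The strongest reply is that shared farms are permitted but never stated. Recruitment is of individuals, through contacts, industry groups, letterbox drops and newspapers. A non-primary user may be a worker or partner who is the only participant from that farm. The reference to farmers and their workers describes the population of interest, not pairs from one property. All of this stands, so the point has to be conditional.

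Three stronger readings are tempting, and the documents support none of them:

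- *That farms are the sampling unit, so the standard errors are certainly too small.* No number of farms is given and the 50 are people. With one person per farm or a zero ICC there is no error. The 17% needs every farm to supply three people and an ICC of 0.5.
- *That the study could lose its power because the effective number falls below 30.* It can fall below 30, but the 1 SD effect needs about 10 farmers and power stays at 94.9% or more in the range shown.
- *That the Pearson and Spearman p values suffer equally.* Inflation there needs farm clustering in both variables and is smaller. For a contrast within a farm, such as primary against non-primary user, ignoring farm would tend to make the standard error too large.

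It can also be said that random effects and the choice of standard error belong in a full plan that a condensed article need not reproduce. That is fair for omitted detail. Here, however, the article does name the model and says that dependence is handled by subject, and it lists the data collected without a farm identifier.

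**Conclusion.** The point holds in conditional form. The entry rules allow several people from one farm or household, the stated model treats people as independent, and no identifier is listed that would show whether it matters. Under assumed values of 1 to 3 people per farm and an ICC of 0 to 0.5, the true standard error of the mean EAChE change is 1.00 to 1.41 times the naive one, and the nominal 5% test has a real level of 5% to 17%. The lower end is more likely, because nothing suggests that every farm supplies several people. At 1.5 people per farm and an ICC of 0.05 to 0.5 the level is 5.3% to 8.0%. The harm is to type I error and interval width. This is a cheap improvement to a stated analysis of a preliminary study, not a defect that undermines it.

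**What to change.** Record a farm/household identifier for every participant at T0, and report the number of farms as well as the number of people. Where farms supply more than one person, analyse the EAChE change with standard errors clustered on farm, or with a farm random intercept on the change.

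Use a small-sample correction with the clustered standard errors. If all 42 or so retained farmers came from farms of two or three participants, there would be only 42 / 2 = 21 or 42 / 3 = 14 farms, and uncorrected cluster-robust standard errors tend to be too small with so few. A full farm-by-time random structure is not required and may not be estimable if most farms supply one person. Enrolling one person per farm would also remove the problem.

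The cost is one field on the baseline form, a sentence in the analysis section, and a slightly wider confidence interval where farms supply several people. If every farm supplies one person, no allowance for farm is needed and the planned analysis stands.

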### Physical assessments and health condition data

A short health history and health behaviours (smoking and alcohol consumption habits) will be obtained from participants with baseline physical assessments of blood pressure measurement (repeated twice), pulse rate, body fat percentage (bioelectrical impedance), respiratory function test (PiKo meter) also measured (see Table 1). Biochemical analysis of EAChE activity using a 10 μl capillary blood sample (measured by Test-mate ChE Cholinesterase tester system Model 400), and EAChE field Assay kit - to establish a baseline reading, will be used (Fig. 1). The Test-mate field assay testing system is based on the Ellman method [18]. Blood glucose and lipids (LDL, HDL) and total cholesterol is also taken after 10-hour fast using the same blood sample.

**Table 1 Tab1:** Data collection description and timeline for farmer and non-farmer groups

Variable	Baseline (T0)	Visit 1 (T1, 1 mth)	Visit 2 (T2, 2 mth)	Visit 3 (T3, 3 mth)
Body weight	✓	X	X	X
Height	✓	X	X	X
Waist circumference	✓	X	X	X
Hip circumference	✓	X	X	X
Body fat %	✓	X	X	X
Blood pressure	✓	X	X	X
Pulse rate	✓	X	X	X
Fasting blood glucose	✓	X	X	X
Fasting blood cholesterol	✓	X	X	X
Fasting triglycerides	✓	X	X	X
HDL cholesterol	✓	X	X	X
LDL cholesterol	✓	X	X	X
Erythrocyte Cholinesterase (EAChE)	✓	✓	✓	✓
Description of monthly chemical use	✓	✓	✓	✓
Kessler (K10)	✓	X	X	X
Chemical Usage Survey	✓	X	X	X

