**Fig. 1 Fig1:**
[figure not shown]
Point of care schedule for cholinesterase assessment

Waist circumference is measured to the nearest 0.1 cm at the end of a normal expiration using a constant tension “Figure Finder Tape Measure”™ [19]. Body Mass Index will be calculated to classify obesity and overweight cut off points for future reference using the WHO parameters [20].

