### Monitoring agrichemical use

In addition to completion of the agrichemical use survey of 13 questions, self-reported chemical use is recorded during each visit. Participants are provided with counselling regarding their EAChE levels in accordance with AgriSafe guidelines (Fig. 2). The USA’s Department of Pesticide Regulation specifies that a drop to 70 % or lower in red blood cell AChE or to 60 % or lower in plasma cholinesterase relative to the individual’s baseline is an indication for immediate removal of the individual from all exposure to organophosphate and carbamate pesticides [25]. Participants will be provided with a summary of their EAChE baseline and subsequent results at the conclusion of the study. This methodology reflects recent exposures and is used to provide feedback at the time of testing. However, it is noted that the level of current exposure is not a measure of long-term exposure and that the clinical parameters around long-term exposure are not well defined.

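### Exposure–metabolic links are to be tested with unadjusted Pearson or Spearman correlations at p < 0.05, without saying how age, sex and farmer/non-farmer group are handled

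*Protocol article*

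**What the plan says.** The section on data entry, handling and statistical analysis names two analyses.

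- The main one: "Data will be analysed using repeated measures (subjects as own controls) within the General Linear Model".
- A second one: "Correlation coefficients between pesticide exposure and metabolic variables will be calculated", using Pearson's or Spearman's coefficient as appropriate.

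One threshold follows for everything: "P values will be considered statistically significant at" p < 0.05. No covariates are named for the correlations. The exposure measure is not defined, the metabolic variables are not listed, and the treatment of the two groups is not stated.

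Other sections supply the context:

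- The abstract's Methods/Design lists "biochemical analysis of fasted total serum cholesterol, triglycerides, low-density cholesterol (LDL), high-density cholesterol (HDL) and blood glucose", which makes five fasting blood measures.
- Table 1 ("Data collection description and timeline for farmer and non-farmer groups") ticks these for T0 only, for example the row "Fasting blood glucose". It ticks erythrocyte cholinesterase (EAChE) and the description of chemical use at all four visits.
- The sample size and inclusions section enrols 50 farmers or contractors who use organophosphates and a convenience sample of 30 non-farmers. Both groups are aged 18 to 75, and no matching is described.
- The section on monitoring agrichemical use warns that "the level of current exposure is not a measure of long-term exposure".

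**The concern.** A simple correlation across people answers the exposure question only if nothing else drives both variables. Here the groups differ in exposure by design, and nothing in the recruitment makes them alike in age or sex. The more-than-five-years farming requirement can apply only to the farmers, which is one documented reason why ages might differ. Lipids and glucose can vary with age and sex, so a coefficient taken across both groups may reflect who was recruited rather than what they were exposed to. Age and sex can also confound within the farmers.

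The repeated-measures model does not rescue this. A variable measured once has no within-person change, and the article does not say that metabolic variables will enter that model as covariates. The metabolic question therefore rests on the correlations. Their p-values may be called significant, with no exploratory label and no limit to recent exposure. A confounded or chance lipid or glucose result could then be read as evidence of an exposure effect.

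**Working it through.** The article gives no number of correlations and no error rate for them, so there is no figure of its own to reproduce. Its sample size concerns the before/after EAChE comparison and does not bear on this point.

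**1. Chance findings across the five blood measures**

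Inputs: 5 measures (abstract, Table 1) and a threshold of 0.05 (analysis section). Assumed: two-sided tests, one exposure measure, no true association.

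- Independent measures: 1 − (1 − 0.05)^5 = 1 − 0.774 = 0.226, or 23%. Expected false positives: 5 × 0.05 = 0.25.
- Correlated measures (simulated, n = 80, 20,000 runs, equal pairwise correlation assumed): 21% at 0.3, 19% at 0.5, 15% at 0.7.

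**2. Confounding by group, if all 80 are analysed together**

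Inputs: 50 and 30 people, so the farmer share is q = 50/80 = 0.625 and v = q(1 − q) = 0.234. Assumed, because the article gives neither: farmers exceed non-farmers by dE within-group SDs on exposure and by dM within-group SDs on a metabolic variable, with zero correlation inside each group.

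Expected coefficient: r = v·dE·dM / √[(1 + v·dE²)(1 + v·dM²)].

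- Low end, dE = 1 and dM = 0.3: 0.0703 / √(1.234 × 1.021) = 0.063.
- High end, dE = 2 and dM = 0.8: 0.375 / √(1.938 × 1.150) = 0.251.

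At n = 80, |r| above 0.220 gives p < 0.05. The table shows the expected r and, in brackets, the simulated share of studies that reject (20,000 runs, nominal 5%).

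| Exposure gap dE | dM = 0.3 | dM = 0.5 | dM = 0.8 |
|---|---|---|---|
| 1 SD | 0.063 (8%) | 0.103 (15%) | 0.157 (29%) |
| 1.5 SD | 0.084 (12%) | 0.138 (24%) | 0.212 (49%) |
| 2 SD | 0.100 (14%) | 0.164 (32%) | 0.251 (63%) |

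The table shows direction and sensitivity; it is not an estimate for this study. If dM is zero, there is no bias from this source.

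**3. What a farmers-only result costs**

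With 50 people the critical |r| at p < 0.05 is 0.279, against 0.220 with 80.

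**The case against.** The strongest reply is that this is a condensed article about a study that calls itself preliminary. The metabolic correlations are not among its aims, and covariates, variable lists and strata for a secondary analysis are commonly left to an analysis plan that is not shown. This stands as far as the missing variable list, the missing exposure definition and the silence on multiplicity go; none of those is a fault by itself. It does not cover the method, because the article names one, and that method is bivariate. The preliminary status supports an exploratory label but does not remove confounding. Excluding known chronic disorders narrows the sample, but leaves age and sex free to differ.

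A reader might also infer stronger points that the text does not support:

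- *That the groups will be pooled.* The article states neither pooling nor separation.
- *That about thirteen variables will be tested, giving a 49% chance of a false positive.* This needs all twelve baseline-only physical and biochemical rows of Table 1, including height and pulse rate, plus one more because "Body Mass Index will be calculated to classify obesity and overweight cut off points". The article never calls these metabolic variables; the five blood measures are the firm count.
- *That four exposure readings will be paired with one metabolic value, counting each person four times.* Nothing proposes this. Table 1 collects both at T0, so one pair per person is the natural reading.
- *That spurious links will occur.* The calculations show that they can, and the confounding part rests on group differences that are not documented.
- *That the caution about long-term exposure invalidates the correlations.* It is a disclosed limit of the EAChE measurement, and the article does not define exposure in the correlations as EAChE.

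**Conclusion.** The concern holds in a limited form. The article fixes unadjusted bivariate coefficients for baseline-only metabolic variables, each judged at p < 0.05, in a sample made of two unmatched groups whose handling is not stated. Age, sex and group composition can create apparent links.

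The size of that bias cannot be stated from the article; the table above shows only what assumed gaps would do. The multiplicity part is firmer but modest: 23% for five independent measures, and about 15–21% under assumed correlations of 0.3–0.7, for a single exposure measure. The before/after EAChE comparison is not affected.

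**What to change.** Amend the correlation sentence in the statistical analysis section so that it:

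- names the exposure measure and the metabolic variables;
- uses the T0 values, one record per person;
- replaces simple coefficients with partial (rank) correlations or regression adjusted for age and sex;
- either adjusts for group or shows a farmers-only result beside the pooled one;
- reports estimates with 95% confidence intervals and labels them exploratory;
- where EAChE is the exposure measure, limits interpretation to recent exposure.

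This needs no new data, since age and gender are already collected. The cost is slightly wider intervals and less exposure contrast once group is adjusted for, because the farmers are selected for organophosphate use. Adjustment for BMI is not asked for, since it may lie on the pathway under study. A formal multiplicity correction is optional once the results are labelled exploratory.

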### Consent and ethics

All adults participating in the study are to be provided with a plain language statement and will provide informed written consent. Ethics approval has been granted to the project by Deakin University Human Research Ethics Committee (HREC 2013-100 dated 18/06/2013). All researchers involved in data collection have a Victorian Police check undertaken.

## Discussion

Organophosphates are still used widely with the actions and attitudes of farmers and workers using these pesticides is vital to their wellbeing and that of their families. It is common for mild to chronic depression of EAChE activity to be reported as ‘normal’ due to the wide reference range for EAChE activity [26]. It is important that farmers and agricultural workers who are routinely using OPs establish their baseline EAChE activity and have access to regular EAChE activity checks for comparison with baseline. Routine monitoring of EAChE may allow for early recognition of frequent and continuous low-level exposure to OPs. This work will provide an evidence base, leading to research to further quantify pesticide exposure both on the farm and in the home of farming families and highlight the importance of sustaining and providing a safe work environment for farming communities.

